## **1. Description of the trial**

This is a single-centre three arm randomised controlled feasibility pilot comparing Parent-Administered Screen Time Intervention (PASTI) against a dummy Bedtime-Box arm and a No-Intervention arm in 17-31-month-old infants who have parent-reported screen time in the hour before bed. Participating families will be recruited from Central/Greater London and surrounding areas and undergo baseline assessments at home and in the lab at the Centre for Brain and Cognitive Development (CBCD) at Birkbeck, University of London. Participants will be randomly allocated (1:1:1) to one of three treatment arms: PASTI, Bedtime-Box, or No-Intervention. Follow-up home and lab assessments will be collected 6-7 weeks after baseline. The main objective of this feasibility trial is to estimate parameters required for planning a definitive trial (e.g. recruitment and randomisation rates). Secondary objectives include obtaining preliminary effect estimates of PASTI on toddler screen time, sleep, and attention control outcomes. More details are provided in the trial protocol.

This statistical analysis plan (SAP) describes the quantitative analyses that will be carried out by the trial statisticians. This does not include qualitative analysis from interviews that will be analysed separately. The statistical analysis plan was drafted and reviewed by blinded trial statisticians per the King's Clinical Trials Unit (KCTU) Standard Operating Procedures (SOP) related to statistical analysis plans [ST-02 Version 3.0]. The trial team will follow KCTU SOPs.

### **1.1 *Principal research objectives to be addressed***

#### **1.1.1 Primary objectives**

The primary aim of the trial is to assess the feasibility of implementing PASTI, compared with a Bedtime Box intervention and No Intervention, in 17-31-month-old infants who have parent-reported screen time in the hour before bed. To fulfil our primary aim, we will:

1. Assess the feasibility of conducting PASTI, including participation rate, participant randomisation, participant attrition, and intervention adherence.
2. Gain insight into parent experiences of PASTI and any barriers to adherence.
3. Estimate statistical parameters of the primary outcomes necessary to power a future large-scale, confirmatory trial, e.g. means and standard deviations of continuous outcome measures: total night-time sleep duration (actigraphy); exogenous attention control (singleton search saccadic reaction time from the Visual Search Task)

#### **1.1.2 Secondary objectives**

Our secondary aims and objectives are to collect preliminary effect size estimates for PASTI's impact on toddler sleep and attention, as well as preliminary effect size estimates for PASTI on secondary sleep (e.g. average nap duration, frequency of night awakenings, sleep onset-latency), attention

(e.g. exogenous and endogenous attention control measures) and screen time outcomes (e.g. average toddler screen use in the hour before bed).

## **1.2 Trial design**

This is a single-centre 1:1:1 randomised controlled trial with three parallel intervention groups, assessing the feasibility of implementing a 7-week Parent-Administered Screen Time Intervention (PASTI) compared to a dummy Bedtime-Box arm and a No-Intervention arm. Descriptions of the trial interventions can be found in the protocol. This feasibility trial will aid in planning a future definitive trial estimating the effect of PASTI on infant attention control and sleep outcomes.

The study assessments take place within the CBCD Babylab and in families' homes. All baseline and follow-up lab assessments will take place in the CBCD Babylab, and all baseline and follow-up home assessments will be completed in each families' home. Families will be allocated to an intervention group and provided with any study material which will be used in each families' home.

### **1.2.1 Participant enrolment**

Families will be recruited via several routes (e.g. CBCD, Early Years Alliance child centres, National Childbirth Trust and Sleep Charity social media platforms and membership databases). Each route will advertise the trial using a physical or online poster that contains a link where families can sign up to take part. Interested families will provide electronic informed consent and complete a pre-screening questionnaire. Study researchers will review the pre-screening questionnaires and contact eligible families to provide full consent for the study and schedule the baseline lab visit.

In the week before the baseline lab visit, participants will undergo baseline home and actigraphy assessments, followed by a baseline lab visit at CBCD. Participants will be randomised at the end of the baseline lab visit by the unblinded researcher.

### **1.2.2 Post-randomisation**

During weeks 1 to 7 after randomisation, participants will complete a bedtime activity diary twice weekly: once on a weekday, and once on a weekend. Participants in the PASTI arm will complete a screen time adherence questionnaire every night during weeks 1 to 7 (except on nights that the bedtime activity diary is administered).

During week 6, after randomisation, participants will complete follow-up home assessments (questionnaires and actigraphy). Participants will attend a follow-up lab visit 7 weeks after randomisation (with a two-week visit window of the expected date).

After the follow-up lab visit in week 7, participants in the PASTI and Bedtime Box arms will be sent a debrief questionnaire.

Baseline and follow-up lab assessments will be conducted by blinded outcome assessors. See Section 1.4 below for further details regarding blinding or refer to the trial protocol.

### **1.3 Eligibility criteria**

After completing the pre-screen questionnaire, participants must meet the following criteria prior to randomisation:

1. A family with an infant between 16 and 30 months at pre-screening (enrolment)
2. A family that lives in Central/Greater London and surrounding areas (within 75 miles of the Birkbeck Babylab)
3. A family who reports that their infant uses screen time in the hour before bed. They must report that their infant uses  $\geq 10$  minutes of screen time in the hour before bed  $\geq 3$  days of the week
4. Caregiver able to provide informed consent.

Reports of screen time use in the hour before bed from baseline questionnaires will not be used to exclude participants that had met eligibility requirements at pre-screening.

Exclusion criteria:

1. An infant with any known genetic or neurological condition (e.g., Downs Syndrome)
2. An infant born prematurely ( $< 37$  weeks)
3. An infant who is taking part in another trial or research study

### **1.4 Randomisation and blinding**

#### **1.4.1 Randomisation**

At the end of the baseline lab visit, participants will be randomised to one of the three treatment arms by the unblinded researcher. Randomisation will be done using an Elsevier web-based randomisation system set up by the King's Clinical Trials Unit (KCTU) at King's College London following KCTU standard operating procedures.

The sequence will be generated using minimisation to ensure balance between trial arms. Minimisation will balance across: child sex, socioeconomic status (IMD quintile), and child age at randomisation (17-24.4 months or 24.5-31 months).

The sequence will be allocated by the unblinded researcher who will enter the participant randomisation details (e.g. child's age, sex, IMD quintile) into the randomisation system and will receive details of the treatment allocation along with a unique participant identifier from the randomisation reference ID that will be used to identify participants in the research database. The unblinded researcher will then inform the participating family of their treatment allocation. Details of treatment allocation will not be shared with the other research staff members. Follow-up outcomes will be assessed by a blinded researcher.

#### **1.4.2 Blinding and planned unblinding**

Due to the nature of the interventions, participants will not be blind to treatment allocation. Participants will be asked not to discuss treatment groups with the blinded outcome assessor.

The junior trial statistician will be blind to the group allocation until trial analysis begins (and at the point of the Statistical Analysis Plan sign off). The chief investigators and the senior statistician will be blind until review of the draft trial report after database lock. The trial steering committee will be blinded and only receive open reports during meetings. The trial steering committee chair may request a closed unblinded report if there are safety concerns.

#### **1.5 Description of intervention period and frequency of follow-up**

The Intervention period in all arms starts from the Monday following the baseline Lab visit and ends at the follow-up Lab visit 7 weeks later. Starting from the week of baseline home assessments and up to the week of the follow-up lab visit, participants will complete twice-weekly activity diaries. Participants in the PASTI arm will also complete brief daily adherence questionnaires in between the baseline and follow-up Lab visits.

#### **1.6 Visit windows**

The follow-up lab visit should occur during week seven of the trial, with a two-week visit window for lab assessments. Questionnaires from baseline and follow-up home assessments (e.g. Brief Infant Sleep Questionnaire, Vineland Adaptive Behavior Scale) should be completed before the corresponding Lab visit.

#### **1.7 Data collection**

All questionnaires will be administered electronically through a web survey platform (REDCap). Data from actigraphy watches and eye-tracking lab assessments will also be captured electronically and processed as described in the protocol. Adverse events are collected through a web-form completed by participants at any point during study participation.

Data collection timepoints are outlined below. Further details of specific measures can be found in the trial protocol, a summary is provided in the Appendix.

| Timepoint/Week (W) #                                           | STUDY PERIOD |           |     |            |                 |    |    |    |    |    |    |           |
|----------------------------------------------------------------|--------------|-----------|-----|------------|-----------------|----|----|----|----|----|----|-----------|
|                                                                | Prescreen    | Enrolment |     | Allocation | Post-allocation |    |    |    |    |    |    | Close-out |
|                                                                | before W0    | W-1       | W0* | W0         | W1              | W2 | W3 | W4 | W5 | W6 | W7 | W7+       |
| ENROLMENT (ALL ARMS)                                    |              |           |     |            |                 |    |    |    |    |    |    |           |
| Informed consent                                               | X            |           |     |            |                 |    |    |    |    |    |    |           |
| Eligibility screening                                          | X            |           |     |            |                 |    |    |    |    |    |    |           |
| Probabilistically sampled                                      | X            |           |     |            |                 |    |    |    |    |    |    |           |
| Allocation (randomised)                                        |              |           |     | X          |                 |    |    |    |    |    |    |           |
| INTERVENTIONS                                           |              |           |     |            |                 |    |    |    |    |    |    |           |
| PASTI Arm                                                      |              |           |     |            | X               | X  | X  | X  | X  | X  | X  |           |
| Bedtime Box Arm                                                |              |           |     |            | X               | X  | X  | X  | X  | X  | X  |           |
| No Intervention Arm                                            |              |           |     |            | X               | X  | X  | X  | X  | X  | X  |           |
| HOME ASSESSMENTS (ALL ARMS)                             |              |           |     |            |                 |    |    |    |    |    |    |           |
| Daytime Activity Levels Questionnaire                          |              | X         |     |            |                 |    |    |    |    | X  |    |           |
| Vineland Adaptive Behavior Scale (VABS)                        |              | X         |     |            |                 |    |    |    |    | X  |    |           |
| Brief Infant Sleep Questionnaire (BISQ)                        |              | X         |     |            |                 |    |    |    |    | X  |    |           |
| Early Childhood Behaviour Questionnaire (ECBQ)                 |              | X         |     |            |                 |    |    |    |    | X  |    |           |
| State and Trait Anxiety Inventory (STAI)                       |              | X         |     |            |                 |    |    |    |    | X  |    |           |
| Sleep Actigraphy watch                                         |              | X         | X   |            |                 |    |    |    |    | X  | X  |           |
| Sleep and Motion Watch Diary                                   |              | X         | X   |            |                 |    |    |    |    | X  | X  |           |
| LAB ASSESSMENTS (ALL ARMS)                              |              |           |     |            |                 |    |    |    |    |    |    |           |
| Mullen Scales of Early Learning                                |              |           | X   |            |                 |    |    |    |    |    | X  |           |
| Visual Search Task                                             |              |           | X   |            |                 |    |    |    |    |    | X  |           |
| Gap-Overlap Task                                               |              |           | X   |            |                 |    |    |    |    |    | X  |           |
| Antisaccade Task                                               |              |           | X   |            |                 |    |    |    |    |    | X  |           |
| OTHER ASSESSMENTS                                       |              |           |     |            |                 |    |    |    |    |    |    |           |
| Daily Screen Time questionnaire (PASTI only)                   |              |           |     |            | X               | X  | X  | X  | X  | X  | X  |           |
| Bedtime Activity Diary (all arms)                              |              | X         | X   |            | X               | X  | X  | X  | X  | X  | X  |           |
| Parent Debrief Questionnaire (PASTI and Bedtime Box arms only) |              |           |     |            |                 |    |    |    |    |    |    | X         |
| Parent Debrief Interview (subset of PASTI arm only)            |              |           |     |            |                 |    |    |    |    |    |    | X         |
| Adverse Events (all arms)                                      |              | X         | X   | X          | X               | X  | X  | X  | X  | X  | X  | X         |

\*Lab measures conducted at baseline lab before randomisation occurs at the end of the visit

## 1.8 Sample size estimation (including clinical significance)

In line with guidance on feasibility studies, no power calculation has been carried out [1]. A sample size of 60 to 100 has been shown to be sufficient in a feasibility trial [2]. A target sample size of 105 (N=35/arm) will be enrolled and randomised.

## 1.9 Primary feasibility and secondary outcome measures

To fulfil the study objectives outlined in Section 1.1, the following outcome measures will be assessed (excluding qualitative analyses for #4 and #5):

### 1.9.1. Primary feasibility outcome measures:

#### 1. Participation rate:

- Number of eligible participants
- Number of participants consenting to the full study
- Proportion of consented participants who are eligible to take part
- Distribution of socioeconomic profiles for families enrolled relative to geographic norms (e.g. Central/Greater London)

In addition, the proportion randomised out of those eligible will be reported.

#### 2. Intervention adherence (in the PASTI arm):

- Average proportion of caregivers that reported no screen time in the hour before bed during the intervention period
3. **Participant retention:**
    - Number and proportion of participants attending the follow-up lab visit out of those randomised overall and by trial arm
    - Number and proportion of participants that complete all follow-up home and lab assessments out of those randomised overall and by trial arm
  4. **Participant experiences:** The distribution of parent experience ratings from debrief surveys completed by PASTI arm participants.
  5. **Assessment acceptability:** The distribution of study assessment acceptability ratings from debrief surveys completed by PASTI arm participants.

The distribution of parent experience ratings and study assessment acceptability ratings from debrief surveys completed by Bedtime Box arm participants will also be summarised.

### 1.9.2 Secondary outcomes:

We will estimate preliminary PASTI effect sizes on the following outcomes at the Weeks 6-7 follow-up home and lab visits:

1. Total infant night-time sleep duration (minutes) using actigraphy (averaged across the 7-9 day actigraphy period immediately preceding the lab visit)
2. Exogenous attention control (single search saccadic reaction time from the Visual Search Task)
3. Average toddler screen use (minutes) in the hour before bed (measured using responses from one weekday and one weekend bedtime activity diary directly preceding the lab visits and with the following formula:  $[\text{average weekday screentime} * 5] + [\text{average weekend screentime} * 2] / 7$ )
4. Additional sleep outcomes:
  - a. Average day-time nap duration (minutes) using actigraphy
  - b. Frequency of night awakenings using actigraphy (averaged across the 7-9 day actigraphy period immediately preceding the lab visit)
  - c. Sleep efficiency (total night time sleep duration expressed as a percentage of time in bed, averaged across the 7-9 day actigraphy period immediately preceding the lab visit) using actigraphy
  - d. Parent-reported sleep onset latency (minutes) from the BISQ-R
5. Additional attention control outcomes (reaction times in milliseconds):
  - a. Prosaccade saccadic reaction time from the Antisaccade Task
  - b. Proportion of antisaccades from the Antisaccade Task
  - c. Baseline saccadic reaction time from the Gap-Overlap Task
  - d. Disengagement saccadic reaction time from the Gap-Overlap Task
  - e. Parent-reported inhibitory control subscale score from the ECBQ
  - f. Parent-reported effortful control global score from the ECBQ

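### Pre-bed screen use (secondary outcome 3) rests on one weekday and one weekend diary night per visit, although both diaries are collected weekly in all arms; pooling two weeks would be a cheap, modest gain in precision

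*SAP*

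**What the plan says.** - **Outcome definition.** SAP Section 1.9.2, item 3, takes average screen use in the hour before bed "measured using responses from one weekday and one weekend bedtime activity diary directly preceding the lab visits". It combines weekday and weekend values with weights 5 and 2 over 7. The plural visits imply the same rule at baseline and follow-up. The section sets the time point as the Weeks 6-7 follow-up.
- **Who is enrolled.** Section 1.3 requires a report of at least 10 "minutes of screen time in the hour before bed" on at least 3 days of the week. It adds that "Reports of screen time use in the hour before bed from baseline questionnaires will not be used to exclude participants" who had met the requirement at pre-screening.
- **What is collected.** Section 1.2.2 says that in weeks 1 to 7 "participants will complete a bedtime activity diary twice weekly: once on a weekday, and once on a weekend". Section 1.5 extends this back to baseline: "Starting from the week of baseline home assessments and up to the week of the follow-up lab visit, participants will complete twice-weekly activity diaries". The schedule in Section 1.7 marks the diary for all arms at W-1, W0 and each of W1 to W7.
- **How it is analysed.** Section 2.6.2.1 gives crude and adjusted mean differences with 95% confidence intervals from linear regression, with the baseline value as a covariate and no p-values.

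The SAP does not use the other diaries for this outcome and gives no reason for taking a single pair. Section 2.8.1 reports only how many diaries were completed.

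**The concern.** Families may qualify with intermittent use: a child at the eligibility floor has no screens on up to 4 of 7 nights. Two sampled nights describe such a child's usual use poorly, and most of the value comes from one weekday night. A family whose habit has not changed can read zero simply because both diaries fell on screen-free nights.

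Screen use is the behaviour that PASTI targets, and Section 1.1.2 names it among the preliminary effect sizes. The daily adherence questionnaire is given to the PASTI arm only, so the diary is the only repeated hour-before-bed record available for comparing arms. What is at stake is precision: a wider confidence interval, a larger SD, more zeros in an outcome analysed by linear regression, and a noisier baseline covariate.

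**Working it through.** The SAP gives no SD, probability or power for this outcome, so there is no figure of its own to reproduce. The weighted mean is taken as (5 × weekday + 2 × weekend)/7.

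**Inputs from the SAP:** one diary of each type per visit; weights 5/7 and 2/7; a floor of 10 minutes on 3 of 7 days; two diaries a week; 35 per arm.

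**Assumptions, not in the SAP:** equal chance of use on each night; nights independent, or exactly k use days placed at random in the week; 10 or 20 minutes on a use night; true between-family SD of 5, 10 or 15 minutes.

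**Chance that both diaries read zero, use unchanged.** Independent nights: (1 − k/7)². Exactly k random days in the sampled week: C(5,k)/C(7,k), because both sampled nights must be non-use nights.

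| Use days per week | Independent nights | Exactly k random days |
|---|---|---|
| 3 | (4/7)² = 32.7% | 10/35 = 28.6% |
| 4 | (3/7)² = 18.4% | 5/35 = 14.3% |
| 5 | (2/7)² = 8.2% | 1/21 = 4.8% |
| 6 | (1/7)² = 2.0% | 0% |
| 7 | 0% | 0% |

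At the 3-day floor with a fixed pattern: three weekdays and no weekend day, 2/5 × 1 = 40%; two weekdays and one weekend day, 3/5 × 1/2 = 30%; one weekday and both weekend days, 4/5 × 0 = 0%.

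With two pairs at the floor, independent nights give (4/7)⁴ = 10.7%, and random days give (10/35)² = 8.2%.

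**Within-family noise at the floor.** With m minutes on a use night, the variance of one night is m² × (3/7) × (4/7). One pair has variance (25 + 4)/49 = 29/49 of that, of which the weekday night supplies 25/29 = 86%. Two pairs halve it.

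- m = 20: night variance 97.96. One pair 57.98 (SD 7.6 min); two pairs 28.99 (SD 5.4 min).
- m = 10: night variance 24.49. One pair 14.49 (SD 3.8 min); two pairs 7.25 (SD 2.7 min).

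**Total SD** = √(between² + within²):

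| Between-family SD | m = 20: one pair → two pairs | m = 10: one pair → two pairs |
|---|---|---|
| 5 | 9.11 → 7.35 (−19%) | 6.28 → 5.68 (−10%) |
| 10 | 12.57 → 11.36 (−10%) | 10.70 → 10.36 (−3%) |
| 15 | 16.82 → 15.94 (−5%) | 15.48 → 15.24 (−2%) |

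**Meaning for the estimate.** With 35 per arm, no attrition and a common SD, the crude 95% half-width is about 1.96 × SD × √(2/35). For between-family SD 10 and m = 20 it moves from 5.9 to 5.3 minutes.

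**Meaning for the covariate.** The share of baseline variance that reflects true differences between families, in the same case, is 100/157.98 = 63% with one pair and 100/128.99 = 78% with two.

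**The case against.** **The single pair may be deliberate.** It lies close to the actigraphy period of 7-9 days before the lab visit, and the section's time point is Weeks 6-7. A longer average, for example one including week 5, would leave that time point and make follow-up unlike baseline. This stands, and it is why the pooling proposed here stops at weeks 6-7. The reason for one pair may also be in the protocol, which was not available for this review.

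**A reader might infer that a third of the sample will read zero by chance.** The SAP does not support that. It gives no distribution of use and no night-to-night correlation. The 29-33% applies only to families at the 3-day floor whose habits are unchanged, and it falls quickly above the floor.

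**A reader might infer a biased treatment effect.** If the sampled nights are representative of weekdays and weekends, the 5:2 mean is unbiased and chance zeros add only noise.

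**A reader might call the SD wrong for planning.** If a definitive trial used the same two-night measure, this SD would be the right one. Section 1.1.1 names sleep duration and singleton-search reaction time, not screen use, as the outcomes whose parameters are to power that trial.

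**A reader might say that the other diaries are thrown away.** They are unused only for this outcome: completion is reported, and the week-4 weekday diary marks the attrition periods. PASTI adherence has its own daily questionnaire and traffic-light metric.

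**The SD gains are near the upper end.** At 3/7 the product p(1 − p) is 12/49 = 0.245, against a maximum of 0.25. Families who use screens nightly, or PASTI families who comply, would show much less of this noise. That also stands.

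**Conclusion.** The point holds as a cheap improvement of minor severity. The outcome samples an intermittent behaviour on two nights, while further diaries from the same follow-up weeks are already scheduled in every arm. The loss is one of precision, not validity: total SD larger than it need be, by an amount that pooling would cut by about 2% to 19% across the assumed ranges, and a weaker baseline covariate. The zero-reading figures depend on the assumed placement of nights and concern unchanged users at the eligibility floor only. No p-values or inferential statements rest on this estimate, so nothing in the trial's primary feasibility conclusions depends on it.

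**What to change.** Redefine outcome 3 in SAP Section 1.9.2, before unblinded analysis:

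- **Follow-up:** all completed bedtime activity diaries in weeks 6-7 before the lab visit.
- **Baseline:** all diaries completed in W-1 and W0 before randomisation.
- **Score:** average the weekday diaries, average the weekend diaries, then combine the two averages 5:2 over 7.
- **Supportive summary:** keep the value from the last weekday and last weekend diary.

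The cost is a few lines of SAP text and minor coding, with no new data and no extra burden on families. The downside is a slightly longer averaging window.

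Where only one pair is available, the gain is small or nil. This may be so at baseline if the W-1 and W0 marks in the schedule describe a single diary week. If the lab visit falls before the week 7 weekend diary, three diaries remain. Most of the gain is kept, since the sampling variance is then (25/2 + 4)/29 = 57% of the one-pair value, against 50% with two full pairs.

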### **2.6.2 Treatment Effects**

#### **2.6.2.1 Continuous outcome data**

Outcomes will be analysed with crude and an adjusted multivariable linear regression analysis. Fixed effects included will be: dummy treatment variables; baseline values of continuous outcomes; minimisation factors (child age group, child sex, family IMD quintile).

The treatment group mean difference (MD) for unstandardised effect sizes and 95% confidence intervals will be presented for both crude and adjusted estimates. Given the sample size and purpose of this feasibility trial, these estimates will not be the basis for inferential statements and p-values will not be reported. The purpose of our effect size estimates is to illustrate the size of effects across a number of possible outcomes.

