### ***Additional measures***

- Adverse events collected throughout study participation via web-form
- Whether or not child has been taking sleep medication, and if child takes sleep medication frequently (asked during lab visits)
- Twice-weekly (one weekday, one weekend) bedtime activity diaries capturing child activities in the hour before bed
- For PASTI and Bedtime Box arms: online debrief questionnaires at the end of the trial examining parent experiences and challenges encountered
- PASTI arm only: short daily screen time adherence questionnaire assessing screen time duration, device, and reason for use

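### The formula for average pre-bed screen use (SAP 1.9.2, item 3) lacks an outer bracket, so as written the 7 divides only the weekend term

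*SAP*

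**What the plan says.** SAP section 1.9.2, item 3, names the outcome as "Average toddler screen use (minutes) in the hour before bed". It is "measured using responses from one weekday and one weekend bedtime activity diary directly preceding the lab visits", combined by a formula with two parts. The first is "average weekday screentime} * 5", closed by its own square bracket. The second, joined by a plus sign, is "average weekend screentime} * 2] / 7". (The curly braces belong to the typesetting, not to the arithmetic.) No bracket encloses the sum of the two parts.

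Appendix 1, under Additional measures, describes the data source as "bedtime activity diaries capturing child activities in the hour before bed". Section 2.6.1 summarises the secondary outcomes at baseline and follow-up. Section 2.6.2.1 adjusts for baseline values and states: "The treatment group mean difference (MD) for unstandardised effect sizes and 95% confidence intervals will be presented". The SAP does not restate or correct the formula anywhere else.

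**The concern.** An average number of minutes within a one-hour window has to lie between 0 and 60. A weighted mean over a week needs weights that sum to 1, here 5/7 and 2/7. The formula as written does not have that property, because the divisor reaches only the second term.

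This is the SAP's only operational definition of its listed between-arm outcome for screen use. The effect is reported unstandardised, so an error of scale in the derived variable would pass straight into the reported difference and its confidence interval. The same derivation would supply the baseline covariate.

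**Working it through.** **Inputs.** WD is the weekday diary value and WE the weekend diary value. Each lies between 0 and 60 minutes, because the diary covers the hour before bed (section 1.9.2; Appendix 1). The multipliers 5 and 2 and the divisor 7 come from section 1.9.2, item 3. The SAP gives no worked value, so there is no stated figure to reproduce.

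**Two readings.**
- As written, with division before addition: 5 × WD + (2 × WE)/7.
- As evidently intended: (5 × WD + 2 × WE)/7.

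**Weights.**
- As written: 5 and 2/7 = 0.286. They sum to 5.286, and the weekday-to-weekend ratio is 5 ÷ (2/7) = 17.5.
- As intended: 5/7 = 0.714 and 2/7 = 0.286. They sum to 1, and the ratio is 5 ÷ 2 = 2.5.

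The weekend weight is the same in both. The whole error sits in the weekday term, which is 7 times too large.

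**Values in minutes.**

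| WD | WE | As written | As intended |
|---|---|---|---|
| 10 | 10 | 50 + 20/7 = 52.9 | 70/7 = 10 |
| 20 | 20 | 100 + 40/7 = 105.7 | 140/7 = 20 |
| 30 | 30 | 150 + 60/7 = 158.6 | 210/7 = 30 |
| 60 | 60 | 300 + 120/7 = 317.1 | 420/7 = 60 |
| 5 | 30 | 25 + 60/7 = 33.6 | 85/7 = 12.1 |
| 0 | 60 | 0 + 120/7 = 17.1 | 120/7 = 17.1 |

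**When the result becomes impossible.** With no weekend use, the written formula exceeds 60 once WD passes 60/5 = 12 minutes. With equal use on both days, it does so above 60/5.286 = 11.4 minutes.

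**Effect on a mean difference.** A true difference of 20 minutes on both days would come out as 5 × 20 + (2 × 20)/7 = 105.7. If weekday and weekend use were equal for every child, the error would be a pure rescaling by 5.286, and a standardised effect would be unchanged. Where they differ, the relative weighting changes as well, so dividing the results by a constant afterwards would not repair them.

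**The case against.** The strongest reply is that nobody would be misled. The word average and the numbers 5, 2 and 7 admit only one sensible meaning. A literal coding would probably show itself early: section 1.3 requires at least 10 reported minutes on at least 3 days a week at pre-screening, so many baseline values would probably exceed 60. Sections 2.13 and 2.14 also provide range and outlier checks. Most of this stands, and it is why the point is minor.

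The checks are not a full safeguard. They do not name this derived variable, and raw diary values between 0 and 60 would pass. A query at 3 SDs would not reveal an error applied to every child, because the SD is inflated too. Low users would also give plausible values, such as 52.9 for a child with 10 minutes on both days.

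A reader might go further and infer three things that the document does not support:
- **That the trial will report values near 317 or a difference near 106.** Those figures arise only under literal coding, and 317 also needs 60 minutes in both diaries. Nothing shows that the formula has been or will be coded that way.
- **That the feasibility verdict is at risk.** None of the five traffic-light metrics in section 2.4 uses this formula. Adherence in the PASTI arm comes from the daily questionnaires.
- **That the future trial's power calculation is at risk.** Section 1.1.1 names night-time sleep duration and saccadic reaction time for that purpose. Section 2.1 does speak more broadly of means and SDs for possible outcomes, but it does not single this one out. Section 2.6.2.1 also rules out inferential use of the effect estimates.

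**Conclusion.** The formula is wrong as written, and its intent is clear. It is a missing outer bracket in the definition of one secondary outcome: a minor but real correction. If it were followed literally, values would be inflated 5.29-fold when weekday and weekend use are equal, would range up to 317.1 instead of 60, and would weight weekday to weekend use 17.5:1 instead of 2.5:1. That would distort the means, SDs, baseline covariate and mean differences for this outcome and no other.

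The conclusion assumes ordinary operator precedence and that the formula is set on one line, as its slash and closed brackets indicate. The size of any harm is conditional on literal coding.

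**What to change.** In SAP section 1.9.2, item 3, write the derivation as ([weekday minutes × 5] + [weekend minutes × 2]) / 7. State that the same code applies at baseline and follow-up. Add a check that the derived value lies between 0 and 60.

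The range check alone would miss low users, so also test the code on an equal pair: 30 and 30 must return 30.

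The cost is one pair of brackets, one sentence and a line or two of code. Data collection, design and the rest of the analysis are unaffected.
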